### Sample size calculation

To detect a relative difference in LoHS of 20% between the mixed ‘PA/MD model’ and solely ‘MD model’, assuming an average LoHS of 7 days [30], alpha 5%, power 80% and an ICC of 0.06 for patients in same ward, 40 wards including 100 patients each are required. Taking into account an expected drop-out rate of 10% at the level of wards, and a 10% drop out rate of patients (withdrawal of informed consent), 44 wards (22 in each arm) with each 115 patients are included. The number of in depth interviews depends on the moment data saturation is attained.

### Data analyses

To compare hospital wards utilizing a mixed ‘PA/MD model’ with wards utilizing a solely ‘MD model’, we use logistic regression analyses for dichotomous outcomes and linear regression analysis for continuous outcomes, both with random coefficients to account for statistical clustering of data in hospital wards. The analysis is on an intention to treat basis and matching will be taken into account. Missing values are substituted by multiple imputation techniques. Multivariable models are constructed to correct for potential confounders. Covariables are included in the final model only if they modify the regression coefficient of ward care model (i.e. the central determinant) by more than 10% (regardless of statistical significance of effects). Explorative subgroup analyses per medical specialism will be conducted for each set of at least six wards with similar specialism are included. All estimates are calculated with 95% confidence intervals.

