## Methods/Design

### Study design and population

A multicenter non-randomized matched-controlled study is performed in The Netherlands, comparing wards utilizing a mixed ‘PA/MD model’ (intervention group) with wards utilizing a solely ‘MD model’ (control group, usual care). Control wards are matched with the intervention wards on the basis of medical specialism and hospital type (i.e. academic versus non-academic). Data collection runs parallel for each pair of matched intervention and control ward, with a maximum deviation of two weeks.

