### Study setting

Hospital wards are being assigned to the intervention group if the PA has completed an accreditated master’s PA degree and covers at least 51% of the available ward care hours per week during dayshifts (8 h-18 h) on weekdays. Wards are assigned to the control group if solely MDs fulfill the hospitalist position. Exclusion criteria at ward level are: 1) Nurse practitioners (including in training) in the role of hospitalist; 2) Only non-graduated PAs in the role of hospitalist; 3) Psychiatric and pediatric wards and intensive care units. In order to enhance the generalizability of findings we include a heterogeneous sample of hospitals across the country and a mix of medical specialism.

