## Discussion

To our knowledge, this is the first multicenter study which investigates the efficacy and effectiveness of reallocation of hospital ward care from MDs to PAs. Most international studies on reallocation of care to PAs are restricted to primary or critical care, limited to one outcome measure, or are of insufficient methodological quality [2].

The major strengths of this study are the multicenter design and the broad view; we perform measurements both at patient, care provider and hospital ward level. A wide variation of instruments and methods is used to obtain data; we use both quantitative measurements (medical patient records, patient and care provider questionnaires, work schedules) and qualitative measurements (semi-structured interviews). As a consequence, we provide not only useful information about the objective effects of reallocation of hospital ward care on a range of outcomes, but we are also able to determine barriers and facilitators for the implementation.

One of the limitations is the non-randomized design of this study. In the Netherlands, PAs followed a so-called ‘dual program’, which means that students are employed within a particular medical specialty while enrolled in the master’s PA program (Table 1). After graduation, PAs are intended to be employed at the same department. The suggestion of randomly relocating the graduated PA to other hospital wards would lead to resistance among the medical specialists who put considerable effort and time to training and supervision.

The non-randomized character of this study implies an increased risk for confounding, which we will take into account in the multivariable analyses. Another challenge is to deal with the heterogeneity of patients across hospital wards. Each hospital differs slightly in determinants like the organization of ward care (care by medical resident or specialist, arrangement of supervision), policies about quality of care, patient case-mix and medical subspecialties, which might reduce explained variation and subsequently reduce the power of this study. When appropriate, we will conduct explorative secondary quantitative and qualitative analyses to explain heterogeneity.

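### Clustering is modelled at ward level only, so if same-arm wards in different matched pairs share a hospital, the interval for length of stay will be too narrow

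*Protocol article*

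**What the plan says.** The Data analyses section specifies linear and logistic regression, "both with random coefficients to account for statistical clustering of data in hospital wards". It adds: "The analysis is on an intention to treat basis and matching will be taken into account". The form of the matching term is not given. The Sample size calculation uses "an ICC of 0.06 for patients in same ward" and has no hospital component.

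On how wards enter the study, Study design and population says: "Control wards are matched with the intervention wards on the basis of medical specialism and hospital type". Hospital type there means academic or non-academic, not the individual hospital. In Study setting, the three ward-level exclusions concern nurse practitioners as hospitalists, wards with only non-graduated PAs, and certain ward types. None limits a hospital to one ward. The same section says "we include a heterogeneous sample of hospitals across the country and a mix of medical specialism" but gives no number of hospitals.

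The Discussion states: "Each hospital differs slightly in determinants like the organization of ward care". It goes on to list quality policy, case-mix and subspecialties.

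**The concern.** The care model is a property of the ward, so the precision of the treatment comparison depends on how many independent wards there are. A ward random effect makes patients on one ward correlated. It does not make two wards of one hospital correlated.

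The matching term does not close this gap in general. Pairs are formed on specialism and academic status, so a surgical PA ward and a cardiology PA ward of one hospital would fall in different pairs. Whatever their hospital contributes to length of stay is then counted twice as if it were independent information.

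Hospital type and teaching status are listed under Confounders, but only as candidates. They stay in the model only if they move the care-model coefficient by more than 10%. That rule addresses confounding; it does not address correlation between wards.

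At stake are the width of the 95% interval and the false-positive rate for the primary outcome.

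**Working it through.** **The plan's own figure.** The Sample size calculation gives 40 wards of 100 patients, a difference of 20% of 7 days (1.4 days), alpha 5%, power 80% and ICC 0.06. The design effect is 1 + 99 × 0.06 = 6.94, so each arm holds 20 × 100 / 6.94 = 288 effective patients. No SD is stated. With two-sided alpha, 288 per arm implies an SD of about 6.0 days, and an SD of 6.0 returns 289 per arm, or 20.06 wards. The figure is therefore plausible but cannot be verified from stated inputs. It treats all 20 wards per arm as independent.

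**Inputs for the check.** From the documents: ICC 0.06, 20 wards per arm and 100 patients per ward. Assumed, because the documents do not give them: the share *h* of the 0.06 that belongs to the hospital (one third, one half, two thirds), and the number *g* of wards per arm that share a hospital two by two. Total variance is set to 1.

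**Formulas, per arm.**
- Variance of the arm mean as the ward-only model sees it: V0 = 0.06/20 + 0.94/2000 = 0.00347.
- Each two-ward hospital adds 2 × 0.06*h* to the variance of the sum over wards. With *g*/2 such hospitals, V = V0 + *g* × 0.06*h* / 400.
- The true SE is √(V/V0) times the model's SE, and alpha = 2Φ(−1.96 / √(V/V0)). The same ratio applies to the difference when both arms have the same layout.

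| Wards per arm sharing (*g*) | *h* | V | V/V0 | SE ratio | True alpha |
|---|---|---|---|---|---|
| 4 of 20 | 1/3 | 0.00367 | 1.058 | 1.028 | 5.7% |
| 4 of 20 | 1/2 | 0.00377 | 1.086 | 1.042 | 6.0% |
| 4 of 20 | 2/3 | 0.00387 | 1.115 | 1.056 | 6.3% |
| 20 of 20 | 1/3 | 0.00447 | 1.288 | 1.135 | 8.4% |
| 20 of 20 | 1/2 | 0.00497 | 1.432 | 1.197 | 10.1% |
| 20 of 20 | 2/3 | 0.00547 | 1.576 | 1.256 | 11.9% |

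**Simulation.** A paired t-test on ward means (40,000 runs), which respects the matching, gave 8.5%, 10.2% and 12.1% when all 20 wards per arm share. With 4 of 20 sharing it gave about 5.5%, 5.9% and 6.2%. The normal approximation is close enough.

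**Layouts with no problem.** If each hospital supplies one ward, the ward effect already contains the hospital effect. Simulated coverage of an unpaired ward-mean t interval (38 df) was then about 95% for hospital shares of 10% to 75%. It was also about 95% with 20 hospitals of two wards each and arms mixed at random.

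**The case against.** The strongest reply is that the problem may not exist. No sentence says that any two wards share a hospital. A countrywide, heterogeneous sample is compatible with one ward per hospital, and the stated model is then adequate. This stands, and it is why the point is conditional. A reader might infer that the planned intervals are wrong as they are, or that the false-positive rate is 8% to 12%. The documents support neither: the second needs every ward in both arms to sit in a two-ward, same-arm hospital.

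A reader might also infer that intervals would be too wide where both wards of a pair come from one hospital. That assumes the pairing is ignored, whereas the plan says it will be taken into account, and a pair term would absorb that shared effect.

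A second reply is that a condensed article may leave the full list of random effects to a longer plan. This has some force, but the article does not leave the cluster level open. It names the ward, and the sample size rests on the same level.

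A third reply is that the Discussion calls the hospital differences slight, and that some of those listed, such as supervision, may vary between wards of one hospital, where the ward effect captures them. That is fair. The hospital share of the ICC is unknown, which is why a range is shown.

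The reassurance from a random mix of arms within hospitals cannot be taken for granted. Study setting assigns wards to an arm by their existing staffing.

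**Conclusion.** The point holds as a conditional weakness of the analysis model. If same-arm wards in different matched pairs share a hospital, the ward-only model overstates precision for length of stay. With modest sharing (4 of 20 wards per arm) the effect is small: an SE understated by 3% to 6%. In the extreme layout it is 14% to 26%. With one ward per hospital, or arms mixed at random within hospitals, there is nothing to correct. These figures rest on the plan's ICC of 0.06, on 20 wards of 100 patients per arm, and on an assumed hospital share of one third to two thirds. The number of wards per hospital decides whether the issue arises, and the documents do not give it.

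**What to change.** Record the hospital of every ward, and report the number of wards per hospital and arm. Add to the Data analyses section that, if any hospital supplies more than one ward, the linear and logistic models include a random intercept for hospital in addition to the ward effect and the matching term. If that variance cannot be estimated, a hospital-clustered sensitivity analysis is reported instead. State that the term drops out when each hospital supplies one ward.

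The change takes a sentence or two and no new patient data, since each ward's hospital is known. Writing it down in advance also avoids choosing the variance structure after the results are seen. The cost is a possibly wider interval, and a weakly estimated hospital variance if only a few hospitals supply several wards.

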### Economic analyses

Discounting of costs and effects is applied as recommended for health economic evaluations in The Netherlands [29]. A comparison is made between the intervention and control group on incremental costs and incremental effects. The incremental cost-effectiveness ratio (ICER) will be calculated as follows: ICER = (Δ costs/Δ effects) where Δ costs represents the difference in annual mean costs between intervention and control group, and Δ effects represents the difference in QALYs between the two groups.

The uncertainty associated with estimates is explored with a bootstrap resampling procedure to produce cost-effectiveness planes as well as targeted one-way sensitivity analyses of potential drivers of key cost (such as type of ward). The bootstrapped ICERs will be presented in a cost-effective acceptability curve displaying the probability that the intervention is cost-effective for a wide range of willingness-to-pay thresholds. P-value is set at 0.05 to indicate statistical significance. To test for several assumptions (i.e. cost-prices and salary), one-way sensitivity analyses will be conducted on the range of extremes.

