### Secondary outcomes

#### Quality of hospital ward care

To assess the quality of ward care, a set of eleven global clinical and process indicators has been selected from the literature and suggestions by a physician panel. The clinical indicators were derived from a national set of indicators for quality of hospital care from the Dutch Health Care Inspectorate (IGZ) [22]. All indicators cover a period of maximum one month after discharge. The selected indicators are:

Clinical indicators:

• Inhospital mortality

• Unplanned transfer to intensive care unit

• Cardiopulmonary resuscitation

• Pressure sore developed during admission

• Fever: number of days body temperature ≥38

• Pain score: number of days Numeric Rating Score ≥7

• Hospital infections: infusion-, urinary track-, airway-, and postoperative wound infections

• Presentation at department of emergency, within one month after discharge

• Non-elective readmission within one month after discharge

Process indicators:

• Days between discharge and letter of discharge

• Introduction hospitalist to the patient less than 24 hours after hospital admission

Data about unplanned readmission and presentation at emergency department after discharge are collected using self-administered patient questionnaires, which are send at one month after discharge date. Information about the other indicators will be retrospectively derived from patient medical records.

#### **
*Patients health-related quality of life*
**

Generic health-related quality of life is measured with the Euroqol-5D (EQ-5D), which is a widely used validated questionnaire containing five domains: mobility, self-care, usual activities, pain, and anxiety/depression [23]. Each domain has three possible levels indicating; no problems, moderate problems or sever problems. Besides, respondents are asked to value their overall health status on a visual analog scale, ranging from 0 (defined as the worst imaginable health state) to 100 (defined as the best imaginable health state). The EQ-5D is assessed by patient questionnaires at three time points: at admission, discharge and one month after discharge.

#### **
*Patient experiences with medical ward care*
**

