### Economic evaluation

To assess the cost implications and efficiency of substitution of hospital ward care from MDs to teams with PAs, an economic evaluation is conducted alongside the outcomes evaluation. This economic evaluation is based on the general principles of a cost-effectiveness analysis, except that the time horizon per included patient is limited to one month after discharge. If equivalence of effects is established the economic decision rule alters in ‘cost minimization’. The primary cost outcome for the economic evaluation is costs associated with the principal admission (LoHS, resource use, consultation of health care suppliers, salaries, productivity loss) and costs that occurred after discharge that is potentially related to hospital ward care (unplanned readmission, presentation at emergency departments, visits of general practitioner, required home care, productivity loss) in a period from admission until one month after discharge (Table 1). The primary effect outcome in the economic evaluation is EQ-5D based QALYs. We will also analyze costs in relation to LoHS, the primary outcome in the outcomes evaluations. Besides these costs and effects, information about patient characteristics such as gender, age, primary diagnoses and co-morbidities are collected in order to account for patient case-mix as far as possible. All patient-related volumes are collected in detail at an individual patient level, primarily from medical patient records and patient and care provider questionnaires. Costs will be calculated by multiplying the volumes of healthcare use with corresponding unit prices, derived from the Dutch Manual for Costing Research [29], which also include organizational overhead costs. All figures will be related to the price level of the same year.

**Table 1 T1:** Volumes included in the economic evaluation

**Volume**	**Unit**
**During hospital stay at the included ward**^ ***** ^	
Length of hospital stay	Number of days
Non-elective transfer to ICU	Number of days
*Resource* use:	
Surgery	Type of surgery
Medication	Frequency, dose and type of medicine
Laboratory tests	Frequency and type of blood test
Radiographic imaging	Frequency and type of radiographic imaging
Scopic tests	Frequency and type of scopic test
Blood components	Number of units
Consultation with health care suppliers^‡^	Number of consultations
*Medical ward staff:*	
Hospitalists	Working hours per week hospitalist

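### The ICER formula calls for annual costs, but costs and QALYs are observed only from admission to one month after discharge; applied literally to costs alone, it would inflate the ratio about tenfold

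*Protocol article*

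**What the plan says.** All statements are in the protocol article.

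- **Economic analyses.** The only ICER formula divides Δ costs by Δ effects. Δ costs "represents the difference in annual mean costs between intervention and control group". Δ effects "represents the difference in QALYs between the two groups", with no period named.
- **Economic evaluation.** Here "the time horizon per included patient is limited to one month after discharge". The primary cost outcome covers the principal admission and potentially related costs after discharge, "in a period from admission until one month after discharge". On the effect side, "The primary effect outcome in the economic evaluation is EQ-5D based QALYs".
- **Table 1.** Volumes are listed under two blocks only: the stay on the included ward and the first month after discharge.
- **Patients health-related quality of life.** The EQ-5D is taken "at three time points: at admission, discharge and one month after discharge".
- **Sample size calculation.** The trial is planned "assuming an average LoHS of 7 days".

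**The concern.** A cost-effectiveness ratio has a meaning only if costs and effects accrue over the same period. Here the numerator is labelled annual, while every description of data collection stops one month after discharge. An analyst who took the formula literally would have to scale an episode of about five weeks up to a year, as though the admission recurred at that rate. Dividing the result by QALYs accrued over the five weeks would give a ratio on a mixed time base.

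At stake is the main economic result. The same section carries the bootstrapped incremental costs and effects into cost-effectiveness planes and an acceptability curve over a range of willingness-to-pay thresholds. A mis-scaled numerator would distort every comparison with a threshold.

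**Working it through.** The article gives no ICER, cost difference or QALY difference, so there is no figure to reproduce. The check compares the two time bases and sizes the mismatch under the literal reading.

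**1. Length of the window.**
- Mean stay: 7 days (planning assumption in the sample size section).
- One month: 28 to 31 days, 30.44 on average.
- Window = 7 + 28 to 7 + 31 = 35 to 38 days, or 5.0 to 5.4 weeks.
- With the average month: 37.44 days, and 37.44 / 365.25 = 0.10 year. The most QALYs a patient with utility at or below 1 can accrue in the window is therefore about 0.10.

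**2. Mismatch factor if costs alone are annualised.** Factor = 365.25 / window in days.

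| Mean stay | Month of 28 days | Month of 30.44 days | Month of 31 days |
|---|---|---|---|
| 3 days (assumed) | 11.8 | 10.9 | 10.7 |
| 7 days (planned) | 10.4 | 9.8 | 9.6 |
| 14 days (assumed) | 8.7 | 8.2 | 8.1 |
| 21 days (assumed) | 7.5 | 7.1 | 7.0 |

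**3. Effect on the ratio.** The article gives no values, so assume a cost difference of 200 euro and a QALY difference of 0.001 per patient, for illustration only.
- Both over the study window: 200 / 0.001 = 200,000 euro per QALY.
- Costs alone annualised: 200 × 9.76 / 0.001 = about 1.95 million euro per QALY.
- Both annualised: (200 × 9.76) / (0.001 × 9.76) = 200,000 euro per QALY. The scaling cancels.

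**4. Effect on the plane and the curve.** Write k for the factor, taken as common to both arms. Each bootstrap point moves from (Δ effects, Δ costs) to (Δ effects, k × Δ costs). Because k is positive, the sign of Δ costs and the quadrant stay the same, so a finding of dominance would stand. For the curve, at threshold λ, the condition λ × Δ effects − k × Δ costs > 0 is the same as (λ / k) × Δ effects − Δ costs > 0. The probability plotted at λ would therefore be the one that belongs at λ / k, about a tenth of the labelled threshold at a 7-day stay.

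**The case against.** The strongest reply is that *annual* is a stray word. The economic evaluation section defines the cost period explicitly, Table 1 lists nothing beyond one month after discharge, and no annualisation step appears anywhere. Costs and effects as collected cover the same window. If the analysis follows that section, the ICER carries no bias of this kind. The formula also names no period for QALYs; if both terms were put on an annual basis, the ratio would be unchanged.

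This reply stands as far as it goes. A reader might infer that the ICER will be wrong by a factor of ten. The article does not support that: the error needs costs to be scaled up and QALYs not, and the text describes neither step.

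The contradiction itself remains. This is the only ICER formula in the article, and it cannot be followed together with the stated horizon. The literal reading is not far-fetched either: in Table 1, hospitalist time and specialist supervision are recorded as hours per week, which are rates rather than amounts per episode, and an analyst could take the formula as an instruction to put such costs on an annual basis.

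A reader might also want the discounting sentence removed ("Discounting of costs and effects is applied as recommended for health economic evaluations in The Netherlands"). Over about five weeks discounting has no practical effect, so removing it would change no result.

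**Conclusion.** The ICER numerator contradicts the article's own horizon and cost period and should be corrected. Applied literally to costs only, with QALYs over the study window, the formula would inflate the ICER 9.6 to 10.4 fold at a 7-day stay, and about 7 to 12 fold for mean stays of 3 to 21 days. The 7 days is the article's planning figure; the wider range of stays is assumed.

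The cost axis of the plane and the acceptability curve would be mis-scaled. Quadrants would not change, given one multiplier for both arms. The size is conditional: it is nil if *annual* is a slip or if both terms are annualised, and the article does not say which is meant. The point concerns the economic evaluation alone. Length of stay as primary outcome, the sample size and the clinical analyses are untouched.

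**What to change.** In the section on economic analyses, replace the annual cost difference by the difference in mean cost per patient from admission to one month after discharge, and state that the QALY difference is taken over that same window. The discounting sentence can stay.

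This changes one sentence and needs no new data and no change to data collection. It should be settled before the economic analysis is run.

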### Confounders

Because of the non-randomized character of this study and the heterogeneity of patients and hospital wards, there is a risk of confounding. We will correct for a number of predefined confounders in the statistical analyses. The covariables related to *patients* are: gender, age, education, ethnicity, marital status, smoking status, body mass index, primary diagnosis, co morbidities, number of prior hospitalizations, type of admission (elective or emergent), discharge destination and the health-related quality of life at admission. *Healthcare provider factors* are gender, age, highest education, profession, years since graduation, years on the job, extent of employment, regularity of work schedules and workload. *Hospital ward characteristics* are medical specialism, hospital type, teaching status, number of admissions, bed occupancy, and number of MDs, PAs and nurses are assessed. Covariables are extracted from patient medical records and patient and care provider questionnaires.

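### The economic analysis does not carry ward clustering, matching and confounder adjustment into the ICER and its bootstrap; if patients are resampled singly, the stated uncertainty is far too narrow

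*Protocol article*

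**What the plan says.** The design is observational at ward level: "A multicenter non-randomized matched-controlled study is performed in The Netherlands". Control wards are matched to intervention wards on specialism and hospital type.

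For the outcomes, Data analyses specifies logistic and linear regression, "both with random coefficients to account for statistical clustering of data in hospital wards". It also says that matching is taken into account and that multivariable models correct for confounding.

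For the economic result, Economic analyses gives its own calculation. The ICER is Δ costs over Δ effects. The numerator is defined thus: "Δ costs represents the difference in annual mean costs between intervention and control group". The denominator is the corresponding QALY difference. Uncertainty is then handled by resampling: "The uncertainty associated with estimates is explored with a bootstrap resampling procedure to produce cost-effectiveness planes". The bootstrapped ICERs also feed the acceptability curve. The section does not mention covariates, matching, wards or the unit that is resampled.

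Two other sections bear on adjustment. Economic evaluation says that patient characteristics "are collected in order to account for patient case-mix as far as possible". Confounders says "We will correct for a number of predefined confounders in the statistical analyses", and its list of patient covariables includes health-related quality of life at admission.

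**The concern.** The care model is a property of the ward, so a comparison of models has the information of about 40 wards, not of 4,000 independent patients. The outcome analysis deals with this through a model. The economic analysis takes its uncertainty from resampling, and a random ward term in a regression does nothing for a bootstrap that ignores wards. Even if each replicate were analysed with a ward random effect, drawing patients singly puts the same 40 wards into nearly every replicate, so variation between wards is never reproduced.

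There is good reason to expect costs to cluster. Length of stay, which was planned with a ward-level ICC, is itself a cost volume in Table 1. Staff input is recorded there as weekly hospitalist hours and weekly supervision hours. Patients on a ward largely share these quantities, and the PA/MD model changes them directly.

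Adjustment has a similar gap. Case-mix data are collected for the economic evaluation, but the stated ICER calculation gives them no place. EQ-5D at admission matters most here, because it enters the QALY directly and the arms are not randomised.

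At stake are the cost-effectiveness plane and the acceptability curve. The curve reports a probability, so understated variance pushes it towards 0 or 1.

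**Working it through.** **Inputs from the protocol article (Sample size calculation).** ICC 0.06 for patients in the same ward, given for length of stay; 40 wards of 100 patients, hence 20 wards per arm; 44 wards of 115 after allowance for drop-out; 20% of 7 days = 1.4 days; alpha 5%, power 80%.

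**Assumptions.** No ICC is given for costs or QALYs, so 0.06 is borrowed and 0.01 to 0.10 is shown as a range. Two-sided alpha is assumed.

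**The plan's own figure.** No numerical result is stated for the economic analysis. The sample size cannot be reproduced outright because the SD of length of stay is not stated, but it can be solved for. With SD 6.0, n per arm without clustering = 2 × (1.96 + 0.84)² × 6.0² / 1.4², which rounds up to 289. The design effect is 1 + (100 − 1) × 0.06 = 6.94. Then 289 × 6.94 = 2,006 per arm, or 20.06 wards of 100. So the stated 20 wards per arm is consistent with a design effect of 6.94 if the SD was about 6.0 days.

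**Effect of resampling patients only.** Such a bootstrap estimates the variance as if all patients were independent. The variance of a difference between ward-level arms is larger by the design effect. Hence:

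- SE ratio = sqrt(1 + (m − 1) × ICC)
- coverage of a nominal 95% interval = 2Φ(1.96 / SE ratio) − 1

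| Patients per ward | ICC | Design effect | SE ratio | Coverage |
|---|---|---|---|---|
| 100 | 0.01 | 1.99 | 1.41 | 84% |
| 100 | 0.06 | 6.94 | 2.63 | 54% |
| 100 | 0.10 | 10.90 | 3.30 | 45% |
| 115 | 0.06 | 7.84 | 2.80 | 52% |

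**Simulation check.** 400 data sets of 20 wards per arm and 100 patients per ward, normal data, 300 bootstrap replicates each, percentile intervals:

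| ICC | Coverage, patients resampled | Coverage, wards resampled |
|---|---|---|
| 0.01 | 86% | 95% |
| 0.06 | 49% | 91% |
| 0.10 | 40.5% | 91% |

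The Monte Carlo standard error near 54% is sqrt(0.54 × 0.46 / 400) = 0.025, so 49% is about two standard errors from the formula.

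**Limits of the figures.** They describe a difference in means for one quantity (costs or QALYs), not the ratio itself. They ignore matching and covariates. If matching on specialism and hospital type, or adjustment, removes part of the ward variation from the comparison, the relevant ICC is lower. The 0.01 row shows that a material shortfall remains even then.

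**The case against.** The strongest reply is that this reads silence as a defect. A difference between intervention and control group is the generic definition of an increment and can be a model-based, adjusted one. The resampling unit is simply not given. Costs and QALYs are continuous, and Data analyses applies ward random coefficients and matching to continuous outcomes without excluding them. A condensed article commonly leaves the cost model and bootstrap details to a fuller document.

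Much of this stands, and it limits what can be claimed. A reader might infer that the plan compares raw group means and that the ICER is therefore confounded. The documents do not support that: Economic evaluation states an intent to account for case-mix, Confounders promises correction without restricting it to clinical outcomes, and quality of life at admission is on the list. A reader might also infer that patients are resampled singly, which is nowhere stated. Nor can a size be put on bias from baseline utility, because the documents give neither an EQ-5D difference at admission nor an expected QALY effect.

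The reply does not remove the point. Economic analyses does more than stay silent: it writes out an estimator and a method for its uncertainty. Regression terms specified elsewhere do not pass into a resampling procedure unless the plan says so. The ordinary bootstrap, run on the text as it stands, would draw patients. The promise of case-mix adjustment and the stated formula are also not joined. Under Data analyses, admission quality of life stays in a model only if it shifts the coefficient by more than 10%, so its place in the QALY comparison is not secured there either.

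**Conclusion.** The point holds in conditional form. As written, the economic section does not carry over the clustering, matching and confounder correction described elsewhere in the article. If the bootstrap resamples individual patients, the SE is understated 2.63-fold and a nominal 95% interval covers about 54%, at 100 patients per ward and ICC 0.06 assumed for costs and QALYs. At an assumed ICC of 0.01 the figures are 1.41-fold and about 84%. Because the section sets significance at 0.05, the same assumptions imply that a null difference would be declared significant about 46% of the time, or 16% at ICC 0.01.

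It is not established that the ICER is confounded or that its intervals are too narrow; both depend on choices that the article does not state. The length-of-stay analysis is unaffected. The section should still be changed, because the economic result is a headline output and the remedy needs no new data.

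**What to change.** In Economic analyses, state three things.

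1. The bootstrap resamples matched pairs, or wards within arm, with patients within the drawn wards as an optional second stage.
2. In each replicate, incremental costs and incremental QALYs come from models adjusted for the predefined confounders, the matching factors and EQ-5D at admission, with the covariate set fixed in advance.
3. The cost-effectiveness plane and the acceptability curve are built from those replicates.

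The cost is some programming and wider intervals. All the data needed are already being collected. With 20 wards per arm, a ward-level percentile bootstrap may still fall somewhat short of 95% (about 91% in the simulation at ICC 0.06), which should be acknowledged when the intervals are reported.
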